## Abstract

**Background:**

Smoking is the world's fourth most common risk factor for disease, the leading preventable cause of death, and it is associated with tremendous social costs. In the Netherlands, the smoking prevalence rate is high. A total of 27.7% of the population over age 15 years smokes. In addition to the direct advantages of smoking cessation for the smoker, parents who quit smoking may also decrease their children's risk of smoking initiation.

**Methods/Design:**

A randomized controlled trial will be conducted to evaluate the effectiveness of proactive telephone counselling to increase smoking cessation rates among smoking parents. A total of 512 smoking parents will be proactively recruited through their children's primary schools and randomly assigned to either proactive telephone counselling or a control condition. Proactive telephone counselling will consist of up to seven counsellor-initiated telephone calls (based on cognitive-behavioural skill building and Motivational Interviewing), distributed over a period of three months. Three supplementary brochures will also be provided. In the control condition, parents will receive a standard brochure to aid smoking cessation. Assessments will take place at baseline, three months after start of the intervention (post-measurement), and twelve months after start of the intervention (follow-up measurement). Primary outcome measures will include sustained abstinence between post-measurement and follow-up measurement and 7-day point prevalence abstinence and 24-hours point prevalence abstinence at both post- and follow-up measurement. Several secondary outcome measures will also be included (e.g., smoking intensity, smoking policies at home). In addition, we will evaluate smoking-related cognitions (e.g., attitudes towards smoking, social norms, self-efficacy, intention to smoke) in 9-12 year old children of smoking parents.

**Discussion:**

This study protocol describes the design of a randomized controlled trial to evaluate the effectiveness of proactive telephone counselling in smoking cessation. It is expected that, in the telephone counseling condition, parental smoking cessation rates will be higher and children's cognitions will be less favorable about smoking compared to the control condition.

**Trial registration:**

The protocol for this study is registered with the Netherlands Trial Register NTR2707.

## Background

Cigarette smoking continues to be a serious problem with detrimental health consequences for the individual and tremendous costs for society [1]. In the Netherlands, the smoking prevalence rate is high, with 27.7% of the population above 15 years smoking [2]. A substantial part of Dutch adult smokers intend to quit smoking in the future [2,3]. Unfortunately, most quit attempts fail, and approximately three-quarters of unaided quitters resume smoking within three months [4].

Several intervention programs have been shown effective in increasing the chance of successful smoking cessation. However, only a minority of smokers makes use of such programs [5,6]. A possible explanation for this low rate may be that most programs rely on the smoker to take the initiative [7]. Proactive recruitment approaches to smoking cessation are scarce, even though such approaches may greatly enhance use of cessation support and, in turn, successful smoking cessation.

In the present study, smoking parents will be proactively recruited through their children's primary schools to participate in a randomized controlled trial evaluating the effectiveness of telephone counselling to aid smoking cessation. Telephone counselling has previously been shown to be effective in increasing smoking cessation rates in a meta-analytic review [8]. A recent Australian study utilized a proactive recruitment approach to increase smokers' use of telephone cessation support. In this study, 52% of identified smokers from a randomly called sample of 48,014 households agreed to participate in a randomized controlled trial to evaluate the effectiveness of telephone counselling in smoking cessation. Participants receiving telephone counselling were significantly more likely to report 7-day point prevalence abstinence at the 4-month (13.8% versus 9.6%) and 7-month assessment (14.3% versus 11%) compared to participants in the control condition [9]. As demonstrated in this study, proactive recruitment into telephone counselling seems an efficient way to increase use of cessation support and to enhance rates of smoking cessation in the general population.

In addition to the direct health benefits for smokers, smoking cessation of parents may have incremental effects for their children. Smoking behaviour of parents is an important risk factor for smoking initiation and smoking behaviour of children. A recent meta-analysis concluded that smoking behaviour of one parent significantly increases the child's risk to initiate smoking, and smoking behaviour of both parents adds to this risk [10]. As nicotine is severely addictive, experimentation with and uptake of smoking is hazardous behaviour. Prevention of children's exposure to factors that increase their risk of smoking initiation constitutes a significant task in tobacco control.

The effects of parental smoking on child smoking are likely to be mediated by children's smoking-related cognitions (e.g., attitudes towards smoking, normative beliefs about smoking, risk and benefit perceptions, tobacco refusal self-efficacy, intention to smoke). Previous research has shown that children of smoking parents are more likely to have more tolerant and positive attitudes towards smoking [11,12], more normative perceptions of smoking [13], and a stronger intention to smoke [12]. Smoking-related cognitions, in turn, have been established as prospective predictors of smoking initiation in adolescents [14,15].

Parental smoking cessation, however, has been shown to constitute an efficient way to decrease children's risk of smoking initiation [16]. The shorter the exposure to family models who smoke, the less likely it is that children will initiate smoking themselves [17]. The effect of parental smoking cessation has been shown to be mediated by their children's cognitions. In a recent study, 49% of the prospective relationship between parental smoking cessation and smoking behaviour of children was significantly mediated by negative attitudes toward smoking and tobacco refusal self-efficacy [18]. Presumably, telephone counseling to aid parental smoking cessation may have measureable effects in children of smoking parents as well.

### Aim and hypotheses

The primary aim of this study is to conduct a 2-arm randomized controlled trial to evaluate the effectiveness of proactive telephone counselling in increasing cessation rates among smoking parents. In addition, we will evaluate differences in smoking-related cognitions among children of parents in the telephone counselling and in the control condition. Three assessments among parents and children will take place (baseline, three months after start of the intervention, and twelve months after start of the intervention). Primarily, we expect higher smoking cessation rates among parents in the telephone counselling condition than in the control condition. Also, we expect children of parents in the telephone counselling condition to have more negative attitudes towards smoking, less normative perceptions of smoking, higher self-effectiveness to refrain from smoking, and a lower intention to start smoking than will children of parents in the control condition.

## Methods/Design

### Study Design

The present study is a 2-arm (telephone counselling versus control condition) randomized controlled trial with three assessments during a period of approximately one year. Participants will be 512 smoking parents and their 9-12 year old children. After giving informed consent and after completing the baseline assessment, 256 parents will be randomly assigned to the telephone counselling condition and 256 parents to the control condition. In the telephone counselling condition, parents will receive up to seven counsellor-initiated telephone calls and three supplementary brochures over a period of approximately three months. In the control condition, parents will receive a standard brochure on smoking cessation. Parent and child assessments will be identical across conditions and take place at baseline, three months after start of the intervention (post-measurement), and twelve months after start of the intervention (follow-up measurement). In both conditions, each parent-child couple will receive an incentive of 100 euro for their participation in all assessments.

### Participants

#### Recruitment

Smoking parents will be recruited through their children's primary schools. Primary school boards will be asked to distribute study invitation letters to all children aged 9-12 years and request that children give these letters to their parents. Study invitation letters include information about the study (e.g., purpose of study, length of the study, frequency of assessments, eligibility criteria). Parents will be able to register for the study by returning a form with their contact information in an enclosed envelope. Registration will also be possible via the study website, via e-mail, or via telephone.

#### Eligibility Criteria

Eligibility criteria are stated clearly in the study invitation letter. Inclusion criteria for the present study are: 1) being at least a weekly smoker, 2) being a parent/caretaker of a child in (Dutch) grade 6-8 (9-12 years old), 3) having the intention to quit smoking (currently or in the near future), and 4) giving informed consent. Upon registration, written informed consent of parents will be obtained. The ethics committee of the Faculty of Social Sciences at the Radboud University Nijmegen approved the study's protocol.

### Randomization

Assignment to a group will be performed by a member of the research group who is not involved in the present study. Participants will be stratified by gender, educational level, and smoking intensity (as reported by participants in the baseline questionnaire). If partners who live in the same household participate in the study, randomization will be carried out at household level to avoid contamination between conditions.

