### Sample size calculation

Based on similar studies, we expected a 6% difference in 7-day point prevalence abstinence rates between the telephone counselling condition and the control condition at 12-months assessment (13% versus 7%, respectively). A statistical power of .80 was targeted. Hypotheses will be tested at a two-sided significance level of .05. The calculated sample size was corrected for participants who will be lost to attrition. Additionally, the sample size was corrected to allow for supplementary analyses of mediation and moderation.

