### Statistical analyses

Analyses will be conducted to check whether the randomization has resulted in an equal baseline distribution of relevant participant characteristics across both conditions. In case of group differences at baseline, confounding variables will be included in subsequent analyses. To evaluate smoking cessation rates across groups, we will use logistic regression models. Effect sizes as well as confidence intervals will be reported. To evaluate smoking-related cognitions across groups (in both parents and children), analyses-of-variance and regression analyses will be used. Mediation and moderation will be tested in Mplus. In accordance with the intent-to-treat principle, all participants randomized to a condition will be included in analyses testing of the study hypotheses. In addition, a complete-case analysis will also be conducted, that is, only participants with outcome data on all assessments will be included in the analysis.

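### Partners who both enrol are randomised as one household, but the named analyses have no household term, so standard errors are somewhat too small if partners' outcomes are positively correlated

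*Protocol article*

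**What the plan says.** All statements are in the Methods/Design part of the protocol article.

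- **Unit of allocation.** Under Randomization: "If partners who live in the same household participate in the study, randomization will be carried out at household level". The reason given there is to prevent contamination between the arms.
- **Strata.** The same section says: "Participants will be stratified by gender, educational level, and smoking intensity". These are characteristics of individuals, taken from each participant's baseline questionnaire.
- **Parent cessation.** Under Statistical analyses: "To evaluate smoking cessation rates across groups, we will use logistic regression models".
- **Cognitions.** Same section: "To evaluate smoking-related cognitions across groups (in both parents and children), analyses-of-variance and regression analyses will be used". Mplus is named only for mediation and moderation.
- **Sample.** Under Study Design: "Participants will be 512 smoking parents and their 9-12 year old children", split as 256 parents per arm, so the count is of individuals. Under Sample size calculation: "Hypotheses will be tested at a two-sided significance level of .05" and "A statistical power of .80 was targeted", with expected abstinence of "13% versus 7%, respectively". The adjustments listed there are for attrition and for mediation and moderation.

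The article does not give the expected number of couples, a within-household correlation, or a rule for which child's data are used when both partners take part.

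**The concern.** Two partners allocated together always share an arm, and there are good reasons to expect their outcomes to move together. The protocol randomises by household precisely because it expects one partner to influence the other. One secondary outcome, smoking restrictions at home, describes the household rather than the person. Ordinary logistic regression, analysis of variance and linear regression take each row as independent information. With positive correlation inside households, they overstate the information in the data, so intervals come out too narrow and p-values too small.

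Child outcomes raise a second possibility. If both partners enrol and both records are linked to the same child, that child would be counted twice. Siblings linked to different partners would be correlated as well.

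There is also a smaller, separate gap. A couple allocated as one unit may straddle the strata: a man and a woman, or partners who differ in education or smoking intensity. No placement rule is stated.

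**Working it through.** **The plan's own figure.** The article gives no design effect to reproduce. Its sample size comes from 13% versus 7%, two-sided alpha 0.05 and power 0.80. The pooled formula gives, per arm:

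n = [1.960 × √(2 × 0.10 × 0.90) + 0.842 × √(0.13 × 0.87 + 0.07 × 0.93)]² / 0.06² = [0.8315 + 0.3553]² / 0.0036 ≈ 391.3, so 392.

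The stated 256 per arm does not follow from these inputs; power at 256 per arm is 62.0%. That is a separate and larger matter. It matters here only because it shows no visible allowance for households hidden in the 512.

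**Design effect.** Let f be the share of participants enrolled with a partner and ICC the within-household correlation. In an arm of N participants, the variance of the outcome total is proportional to N(1 − f) + Nf(1 + ICC) = N(1 + f × ICC). Hence:

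- DE = 1 + f × ICC
- the correct standard error is √DE times the one that ignores households
- actual two-sided alpha = 2 × [1 − Φ(1.960/√DE)]

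Neither f nor ICC is in the article. Every value below is an assumption.

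| f | ICC | DE | √DE | Actual alpha |
|---|---|---|---|---|
| 5% | 0.3 | 1.015 | 1.008 | 0.052 |
| 20% | 0.1 | 1.02 | 1.010 | 0.052 |
| 10% | 0.3 | 1.03 | 1.015 | 0.0535 |
| 20% | 0.3 | 1.06 | 1.030 | 0.057 |
| 30% | 0.3 | 1.09 | 1.044 | 0.0605 |
| 40% | 0.5 | 1.20 | 1.095 | 0.074 |

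**Power.** At f = 20% and ICC = 0.3, the 256 per arm are worth 256/1.06 = 241.5 independent participants. Power for 13% versus 7% falls from 62.0% to 59.4%.

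**Child outcomes, worst case.** If every enrolled couple shared one child and that child were entered twice, ICC would be 1 and DE = 1 + f. The actual alpha would be 0.056 at f = 5%, 0.074 at f = 20% and 0.110 at f = 50%. If each child is entered once, this extra inflation disappears.

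**The case against.** The best reply is that this reads too much into a condensed article. The Statistical analyses section names model families in a sentence each. It does not say that observations are independent or how variances will be estimated. A logistic regression with household-robust standard errors is still a logistic regression, Mplus can handle clustering, and an analysis plan that is not shown may settle the matter. This stands to the extent that a reader might infer that the plan treats every parent and child as independent, and the documents do not support that. The household rule is conditional, only households with two participating partners are touched, and independence is never asserted. What the reply does not remove is that the article states a clustered allocation and names analyses that, followed as written, ignore it.

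The second reply concerns size, and it stands. Few couples mean little inflation. An ICC of 0.3 is also demanding for a rare outcome. At 10% abstinence (the midpoint of 13% and 7%), it implies that a quitter's partner is abstinent with probability 0.10 + 0.3 × 0.90 = 37%; an ICC of 0.5 implies 0.10 + 0.5 × 0.90 = 55%. The 0.074 for parent outcomes belongs to the far end of the range.

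Third, a reader might infer that children are in fact counted twice. No text says so; the article speaks of parent-child pairs and is silent on shared children. Duplication is a possibility to exclude, not an established fault.

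Fourth, a reader might infer that the strata cannot be applied to mixed couples at all. That is too strong, since simple rules would work. The rule is merely unstated, and its absence may cost a little balance but does not bias a randomised comparison.

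**Conclusion.** The point holds in conditional form. Allocation is by household for couples, while neither the named analyses nor the listed sample-size adjustments reflect this. If partners' outcomes are positively correlated, standard errors from the models as named are too small. For parent outcomes the effect is probably modest: alpha is about 0.052 to 0.057 for f between 5% and 20% at an ICC of 0.3, reaching 0.074 only at f = 40% and ICC = 0.5. For child outcomes the design effect could reach 1 + f, but only if the same child sits in both partners' records. All of this rests on assumed f and ICC, so the article does not support a flat statement that the intervals are too narrow by a given amount. The change is worth making because the error runs in the anti-conservative direction and the remedy uses information the trial already holds. The stratification gap is secondary and needs only clarification.

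**What to change.** 1. State that the logistic and linear models for parent and child outcomes use household-clustered standard errors (robust or GEE), with a participant enrolled without a partner forming a household of one. There would be between 256 households (everyone paired) and 512 (no pairs), enough for such standard errors to be stable.
2. Enter each child once in the child analyses, with a rule set in advance for which parent's record carries a shared child, and keep siblings within their household cluster.
3. Report the number of households with two participating partners.
4. State how couples were placed in the strata, for example by the parent who registered first or in a separate couple stratum.

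The cost is a few sentences in the analysis plan and one option in the model code, since household is already known from the allocation. The downside is slightly wider intervals: about 3% wider at f = 20% and ICC = 0.3, and about 1% or less if couples make up 5% of participants at the same ICC.

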### Sample size calculation

Based on similar studies, we expected a 6% difference in 7-day point prevalence abstinence rates between the telephone counselling condition and the control condition at 12-months assessment (13% versus 7%, respectively). A statistical power of .80 was targeted. Hypotheses will be tested at a two-sided significance level of .05. The calculated sample size was corrected for participants who will be lost to attrition. Additionally, the sample size was corrected to allow for supplementary analyses of mediation and moderation.

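### The printed design inputs need about 391 parents per arm before any correction; the planned 256 per arm give about 62% power, not 80%

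*Protocol article*

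**What the plan says.** The Sample size calculation section of the protocol article gives every input of a two-proportion calculation. For the effect: "we expected a 6% difference in 7-day point prevalence abstinence rates", placed "at 12-months assessment (13% versus 7%, respectively" for counselling and control. For the error rates: "A statistical power of .80 was targeted" and "Hypotheses will be tested at a two-sided significance level of .05".

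Two upward adjustments are then claimed: "The calculated sample size was corrected for participants who will be lost to attrition", and in addition "the sample size was corrected to allow for supplementary analyses of mediation and moderation". Neither the uncorrected number nor the size of either adjustment is printed.

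The final number is in the Abstract (512 in total) and in Study Design: "256 parents will be randomly assigned to the telephone counselling condition and 256 parents to the control condition". The Statistical analyses section compares cessation rates by logistic regression and keeps all randomized participants in the tests of the hypotheses.

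**The concern.** A number that has been increased twice cannot be smaller than its starting point. For low event rates and a 6-point difference, 256 per arm looked too small even as the starting point.

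The sizing endpoint, 7-day abstinence at 12 months, is one of the primary outcomes. If the planned effect is real and power is well under 80%, the trial is much more likely to miss it than the article tells the reader, and a null result may be taken as coming from an 80%-power trial. The text also presents mediation and moderation as allowed for in the size, which gives those analyses more standing than the numbers support.

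**Working it through.** **Inputs** (Sample size calculation and Study Design): p1 = 0.13, p2 = 0.07, difference 0.06, mean rate 0.10; two-sided .05, so z = 1.960; power .80, so z = 0.8416; 256 per arm, allocated 1:1.

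**Step 1. Try to reproduce the planned size.** Pooled two-proportion formula:

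n = [1.960·√(2·0.10·0.90) + 0.8416·√(0.13·0.87 + 0.07·0.93)]² / 0.06²

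= (0.8315 + 0.3553)² / 0.0036 = 391.3 per arm, so 392 (784 in total).

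The plan's 256 is about 65% of this (256/391.3), and this is the requirement with no attrition.

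**Step 2. Look for another standard reading that gives 256.** Required number per arm, rounded up:

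| Method | Two-sided .05 | One-sided .05 |
|---|---|---|
| Pooled | 392 | 309 |
| Unpooled | 389 | 307 |
| Arcsine | 384 | 303 |
| Log odds ratio | 404 | 319 |
| Continuity-corrected | 424 | 341 |

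None gives 256 or fewer, and the one-sided column contradicts the stated two-sided test. A correction for attrition only widens the gap: an assumed 10% or 20% loss raises 391.3 to 391.3/0.9 = 435 or 391.3/0.8 = 489 per arm (each rounded up to whole parents where needed).

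**Step 3. Power of the planned size.** At 256 per arm the standard error is √(2·0.10·0.90/256) = 0.02652 under no difference and √(0.1782/256) = 0.02638 under the planned difference.

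Power = Φ[(0.06 − 1.960·0.02652)/0.02638] = Φ(0.304) = 0.62.

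Exact enumeration of the Pearson chi-square test gives 0.623. Simulation with 200,000 replicates gives 0.62 for both the chi-square and the logistic Wald test.

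**Step 4. Effect of attrition.** The article gives no rate, so this is an assumed range, with lost participants leaving the analysis:

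| Lost | Power for 13% vs 7% |
|---|---|
| 0% | 0.62 |
| 10% | 0.57 |
| 20% | 0.53 |
| 30% | 0.47 |

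**Step 5. Detectable difference.** Solving the same power formula for p1 with p2 = 0.07 and power 0.80 gives 14.7% (7.7 points) at 256 per arm and 15.8% (8.8 points) at 205 per arm, which is 256 less 20%.

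**Context only.** The proactive-recruitment trial described in the Background reported, at its "7-month assessment (14.3% versus 11%) compared to participants in the control condition", a 3.3-point difference, and 13.8% versus 9.6% at 4 months. Power for these differences at 256 per arm is about 0.20 and 0.31. This bears on whether 6 points is cautious; the arithmetic above does not depend on it.

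**The case against.** The strongest objection is that the figures disagree without showing which one is wrong. A misprinted rate is possible. Purely as illustration, 13% versus 5% needs about 200 per arm and 15% versus 7% about 239, and either would leave some room below 256 for a correction. On that view the authors may really have made their corrections from a different base, and it goes too far to say that none was made. This stands in part: what can be said is that no allowance exists under the printed inputs. If other inputs were used, the section is still wrong as printed.

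The attrition figures are also conditional. All randomized participants are to be analysed, and if missing outcomes were counted as smoking and 13% and 7% are rates on that basis, the denominator stays at 256. That is correct, but power is then 62%, still far from 80%.

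The cited trial recruited by random household calls and was assessed earlier, whereas this trial requires an intention to quit and is sized at 12 months. The comparison is therefore context and not evidence of the error.

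The article says that .80 was targeted, not that 512 achieves it. But it describes a size calculated for that target and then corrected, and 512 is the only size given, so a reader will take it as delivering at least 80%. It is also true that the article already calls mediation and moderation supplementary and promises confidence intervals, so those parts of the remedy ask for little.

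Finally, an article condenses a fuller protocol. That excuses missing detail, but not printed inputs and a printed size that contradict each other.

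**Conclusion.** The concern holds. Under the stated inputs the uncorrected requirement is about 391 per arm (384 to 424 across two-sided methods), against 256 planned. Power at 256 per arm is about 62% with no loss, so a true effect of the planned size would be missed in about 38 of 100 such trials. With an assumed 20% to 30% leaving the analysis, it would be missed in about half (power 0.53 to 0.47).

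Under these inputs 512 cannot contain any allowance for attrition, mediation or moderation. The 62% rests only on printed figures and independent observations; randomizing participating partners together by household could only lower the effective size slightly further. The figures below 62% rest on assumed attrition. The stated power must be corrected before the section can stand.

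**What to change.** Keep 512 and restate what it provides. Suggested wording: 'With 256 parents per arm the trial has about 62% power (about 53% if 20% are lost from the analysis) to detect 13% versus 7% abstinence at a two-sided level of .05; 80% power is reached for about 14.7% versus 7%.' The 20% is an assumption, to be replaced by the sponsor's own expected rate.

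Remove the statement that the size was increased for attrition and for mediation and moderation, label the mediation and moderation analyses exploratory, and rest the 12-month conclusion on the confidence interval for the difference.

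If the sponsor holds different inputs that led to 512, print those instead, with the uncorrected number and the size of each correction, so that the calculation can be reproduced.

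The cost is wording in the sample size section and a less favourable stated power. No extra participants and no change to trial conduct are needed.
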